**Summary**

Intermittent preventive treatment (IPT) offers a potential way of preventing malaria infection without compromising the development of malaria immunity or encouraging drug resistance. The effect of IPT in children in the prevention of malaria has been evaluated in a number of trials in areas of seasonal malaria transmission. Results from these trials have shown that IPTc provided between 40% - 86% protection against clinical malaria. In 2006, a trial that compared two methods of IPTc delivery was carried out in Upper River Division, The Gambia. Preliminary results of the trial have shown that the treatment was very effective as only 4% (45/1133) of the children seen at the end of year cross-sectional survey were parasitaemic. Tolerability was assessed in a subset of 1100 children and the results showed that about 13.5% of children developed mild to moderate vomiting. Malaise was present in about 10% of the study subjects. Severe adverse events were rare. Thus it is important to investigate if other drug regimens might be equally effective in preventing malaria but less likely to cause adverse events. During the 2007 malaria transmission season, 1009 children aged 1-5 years will be individually randomized to receive amodiaquine plus SP, piperaquine plus SP or Artekin TM (dihdroartemisinin plus piperaquine) at monthly intervals on three occasions during the months of September, October, and November. To determine the prevalence of side effects following drug administration participants in each treatment group will be visited at home three and seven days after each round of drug administration and a side effects questionnaire completed. To help establish whether these adverse events are drug related, the same questionnaire will be administered after each treatment round, to 286 age-matched children who are not part of the trial. The primary ends points will be the incidence of adverse events.

1.0 Background

*1.1 Malaria control in Sub-Saharan Africa*

Although tremendous advances have been made in controlling malaria during the last two decades, the disease remains a major killer in sub-Saharan Africa. Malaria is estimated to cause over one million deaths a year and the vast majority of deaths occur among young children, especially in remote rural areas of Africa (WHO 2000). Community based trials with insecticide-treated bednets (ITN) , which started in the late 1980s in The Gambia and elsewhere, achieved a 40 to 60% short term-reduction in malaria mortality in children less than 5 years in areas with high coverage (Alonso et al. 1993; Greenwood and Pickering 1993). However, achieving high levels of coverage with ITN has proved difficult and other control strategies are needed. Anti malarial chemoprophylaxis for the whole paediatric population has been shown to reduce malaria morbidity and all cause mortality but this strategy is not generally encouraged due to the threat of resistance and difficulties in implementation (Laing , 1984; Pringle and Avery-Jones, 1966; Greenwood, 2004). Chemoprophylaxis can also result in loss of acquired immunity or a delay in the development of clinical immunity leading to a period of increased risk of clinical malaria on cessation of the intervention. Intermittent preventive treatment offers a potential way of preventing malaria infection without compromising the development of malaria immunity or encouraging drug resistance. Use of drugs in combination for IPT may help to prevent selection for resistance.

*1.2. Intermittent preventive treatment*

*1.2.1 Definition*

IPT can be defined as drug administration, in curative doses, given at specific opportunities (for example ante-natal visits or routine vaccinations), with the objective of preventing malaria. Drugs are provided irrespective of the presence of parasites or symptoms. Drugs used for IPT must be very safe as well as effective.

*1.2.2 Intermittent preventive treatment in infants (IPTi)*

The concept of IPT was initially developed for the control of malaria in pregnancy and the administration of SP on two occasions during the second and third trimesters of pregnancy is now recommended practice in areas of medium or high malaria risk where SP resistance is still uncommon (Parise et al., 1998; Shulman et al., 1999). This approach was subsequently adapted to the prevention of malaria in Tanzanian infants. In a study in Tanzania in infants, three doses of SP given at the time of vaccinations with DPT2, DPT3 and measles vaccine reduced the rate of clinical malaria by 59% and that of severe anaemia by 50% during the first year of life in an area of intense transmission (Schellenberg et al., 1997).Significantly, this protective effect persisted up to the age of 24 months (Schellenberg et al., 2005). In a trial conducted in another part of Tanzania, IPT with amodiaquine provided 65% protection against malaria fevers and 67% protection against anaemia without evidence of subsequent rebound (Massaga et al., 2003).However, different results were obtained in a study undertaken in northern Ghana where malaria transmission is intense and seasonal. Significant levels of protection against clinical attacks of malaria (25%) and episodes of anaemia (35%) were observed during the first year of life but more episodes, especially those associated with high density parasitaemia, occurred in children who had received IPT than in controls during eight months period which commenced three months after the last dose of IPT had been given (Chandramohan *et al.,* 2005). Overall, IPT provided only 12% protection against episodes of anaemia during the first two years of life. In a more recent trial conducted in southern Mozambique, an area with perennial transmission, IPTi during the ﬁrst year of life reduced the incidence of clinical malaria by 22 % and the rate of hospital admissions by 19%. However, the intervention did not have any significant effect on the incidence of severe anaemia (packed cell volume of < 25%) [Macete *et al.,* 2006] . Results from two further trials conducted in Ghana (submitted for publication) have given results similar to those found in the study of Chandramohan et al. (2005), about 25% protection against clinical attacks of malaria. No other trials have observed the sustained protection seen in the first study conducted in Tanzania and in each of the more recent studies conducted in Ghana there has been some suggestion of a rebound in the year after treatment was give. Evidence from the more recent trials suggests that the effectiveness of SP in IPTi depends upon its chemoprophylactic effect.

***1.2.3 IPT in children (IPTc).***

In areas of intense malaria transmission a high proportion of the mortality and severe morbidity due to the infection occurs during infancy. IPTi could have a significant impact on overall malaria morbidity in childhood in such communities. In contrast, in areas of seasonal transmission, the major burden of malaria is not in infants but in older children. In such areas, IPTi alone is not likely to have a major impact on the overall burden of malaria. For IPT to have a significant impact on malaria mortality and morbidity in such areas it needs to be given to children as well as infants.

The role of IPTc in the prevention of malaria and anaemia has been evaluated in a limited number of trials. In Mali, an area of seasonal malaria transmission, two doses of SP given to children aged 6 months to 9 years at an interval of two months gave a protective efficacy of 40% against clinical attacks of malaria among children in the intervention group compared to the placebo group (Dicko et al, 2004). In another, study in Niakhar, Senegal IPTc in an area of intense but short seasonal malaria transmission, SP and one dose of artesunate given to children less than 5 years old three times at one monthly interval throughout the peak period of malaria transmission season resulted in an 86% reduction in clinical malaria (Cissé B et al, 2006). Thus, these results suggest that IPTc has potential as an affordable malaria and anaemia control tool in areas of seasonal transmission.

It is not certain whether IPTc could be effectively delivered through the infrastructure of the Reproductive and Child Health (RCH) service given the ever increasing workload of the RCH clinics. With support from the Gates Malaria Partnership, a study to compare two strategies for the delivery of intermittent preventive treatment in children was undertaken in 2006 in 14000 children in Upper River Division of The Gambia where malaria transmission is seasonal. Twenty-six RCH trekking clinics in Upper River Division were randomly allocated to receive IPT from the RCH trekking team or from a village health worker. Treatment with a single dose of sulfadoxine /pyrimethamine (SP) plus three doses of amodiaquine was given to all study subjects at monthly intervals on three occasions during the months of September, October and November. Preliminary analysis of the results showed that the treatment was very effective as only 4% (45/1133) of the children seen at the end of year cross-sectional survey were parasitaemic. Compliance was initially high but decreased progressively with increase in the number of doses taken by the study subjects. 81%, 74% and 67% of study subjects in the VHW arm received IPT during September, October and November respectively. In the RCH arm, 69%, 51% and 48% received IPT during September, October, and November respectively. Tolerability was assessed in a subset of 1100 children and the results showed that about 13.5% of children developed mild to moderate vomiting but there was no control group for comparison. Mild to moderate malaise was present in about 10% of the study subjects. Severe adverse event was rare. However, these adverse events had a negative impact on compliance because of the perception among the study population that the trial medication was associated with a significant number of adverse events. Thus, it is important to investigate if other drug combinations might be equally effective in preventing malaria but more effective in preventing adverse events. Thus, we now propose to compare the safety, efficacy and tolerability of three potential drugs combinations for IPTc. The drugs combinations that we have selected for comparison are amodiaquine plus sulfadoxine-pyrimethamine (the combination used in the previous study), sulfadoxine-pyrimethamine plus piperaquine (another long acting drug) and Artekin TM (dihydoartemsinin plus piperaquine).

*1.2.4 Potential drugs for use in IPT*

Amodiaquine

Amodiaquine (AQ) is a 4-aminoquinoline antimalarial drug similar in structure and activity to chloroquine with antipyretic and anti-inflammatory properties. It is rapidly converted to the metabolite DEAQ and the antiparasitic effect is mainly attributed to this metabolite. A review of published and unpublished studies conducted in Africa on the treatment of uncomplicated falciparum malaria showed that AQ is significantly more effective than chloroquine (CQ) in clearing parasites, with a tendency for faster clinical recovery (Olliaro et al., 1996). The most common adverse reactions to AQ when it is given in therapeutic doses for malaria treatment are nausea, vomiting, abdominal pain, diarrhoea and itching and a less common effect is bradycardia (Brasseur et al., 1995, Sowunmi et al., 2001). When used for chemoprophylaxis in Caucasians, AQ caused toxic hepatitis and fatal agranulocytosis. The incidence of serious reactions in UK travellers using AQ for prophylaxis was 1 in 1 700. Blood disorders occurred in 1 in 2 200 travellers and serious hepatic disorders in 1 in 15 650. Fatal events occurred in 1 in 15 500 travellers (Phillips-Howard et al., 1990). However, AQ has been used extensively in Africa for the treatment of malaria, especially in francophone Africa, with few reports of serious adverse effects.

Sulphadoxine-pyrimethamine

Sulphadoxine-pyrimethamine (SP) is an antifolate combination drug, which acts by synergism against the parasite-specific enzymes, dihydropteroate synthetase and dihydrofolate reductase. It is an effective blood schizonticide against *P. falciparum* but less effective against other species of plasmodium. It does not show cross-resistance with the 4-aminoquinolines, mefloquine, quinine, halofantrine or the artemisinin derivatives. It has a long half-life, hence its formulation as a single dose drug, which is why compliance to it is high. SP has been used successfully in areas with highly developed *P. falciparum* resistance to chloroquine and during malaria epidemics. However, the long half-life of SP provides a potent selective pressure for parasite resistance in areas of high transmission. Therapeutic doses of SP for malaria are generally well tolerated. The most serious adverse reactions are associated with hypersensitivity to the sulphadoxine component, involving the skin and mucous membranes, normally occurring after repeated administration. A high incidence of cutaneous side effects precluded the use of SP for prophylaxis in Caucasian travellers. However serious cutaneous reactions following single-dose treatment with SP are rare and analysis of the large data base on the safety of SP when used for IPTi carried out by the IPTi Consortium has shown that SP is very safe when used for IPT in infants.

Amodiaquine/sulphadoxine-pyrimethamine (AQ/SP) combination

A systematic review and meta-analysis of seven randomised trials on the comparative efficacy and safety of AQ plus SP and artemisinin-based combinations for the treatment of uncomplicated falciparum malaria in African children showed that treatment failures were significantly fewer following treatment with AQ plus SP than after treatment with artesunate (AS) plus SP but were increased compared with Coartem, and similar compared with AQ plus AS. The incidence of serious adverse events was similar in all the treatment arms, although the numbers were small (Obonyo et al 2006). A trial undertaken in Senegal in 2004 children compared different treatment regimens for IPTc . The combinations investigated were SP plus one dose of artesunate, SP plus three doses of artesunate, SP plus three doses of AQ and three doses of AS and AQ. The children were visited after each treatment to record any adverse events and were kept under weekly malaria surveillance throughout the 2004 malaria season. The best results were obtained with SP plus AQ. This regimen showed the highest level of protection against infection and the lowest prevalence of parasitaemia at the end of the malaria transmission season. The main side effects recorded were fever, vomiting, agitation and headache. Each of these symptoms was seen more frequently in children who took SP plus AQ than in children in the SP plus AS groups, but the overall incidence was low (Sokhna et al. submitted).

Piperaquine

Piperaquine (PQP) is an orally active bisquinoline developed for clinical use in China in 1973(Wang et al., 1981, Yin et al., 1981, Yang et al., 1992, Lan et al., 1989, Chen et al., 1981, Shen et al., 1981). The phosphate salt is water-soluble. *In-vitro* testing in several laboratories has shown that PQP is approximately equivalent to CQ against sensitive parasites and significantly more effective than CQ against resistant *P.falciparum.* Like other members of this class of antimalarials, PQP chemically inhibits haem bio-crystallisation. The estimated terminal elimination half-life is approximately 17 days, but only limited pharmacokinetic (PK) data are available in man (Hung et al., 2003). The gastrointestinal side effects of PQP are similar to those of chloroquine but milder at total doses of less than 2g. Otherwise the toxicity profile is similar. PQP replaced CQ as recommended treatment for *falciparum* malaria in China in 1978. Over the next 14 years, 214 tons of PQP equivalent to 140,000,000 adult doses, were used for mass prophylaxis and treatment. Thus, in terms of drug treatment administered, PQP is amongst the most widely used antimalarial drugs in the world. Surveillance at the time found no adverse events other than rare cases of rash.

Dihydroartemisinin

Dihydroartemisinin (DHA) is the active metabolite of AS and artemether, and manufactured as an oral antimalarial drug in its own right in China. It has equivalent clinical efficacy to the more widely used artesunate. The mode of antimalarial action of this class of compounds is thought to involve intraparasitic Fe++ catalysed production of carbon centred free radicals. Recently, an alternative mode of action for the artemisinins has been reported involving irreversible inhibition of a metabolic enzyme - the malarial calcium-dependent ATPase (PfATP6). PfATP6 is very similar to a mammalian ATPase (the sarco/endoplasmic reticulum calcium-dependent ATPase, SERCA), which is located in the sarco/endoplasmic reticulum (ER) (Eckstein-Ludwig et al., 2003). DHA is absorbed and eliminated rapidly (t1/2 circa 45 min.). To date no significant resistance has been reported and stable high level resistance cannot be induced in the laboratory. These drugs are extremely safe in clinical use; there is no evidence that they produce neurotoxicity, or any other systematic toxic effects at therapeutic doses (Price et al., 1999, Looareesuwan et al., 1996). The only significant adverse effect is rare idiosynchratic type 1 hypersensitivity reactions (Leonardi et al., 2001). In experimental animals with early pregnancies, fetal toxicity leading usually to fetal resorption occurs with high doses of the artemisinin derivatives and some surviving embryos have congenital abnormalities. Clinical experience in pregnancy to date has shown no cause for concern (McGready et al., 2001). A recent WHO consensus committee concluded these drugs could be used in the second and third trimesters, but pending further information, not in the first trimester of pregnancy unless the life of the mother was at risk and no effective alternative was available(*WHO TDR/RBM 2002)*.

ArtekinTM

Dihydroartemisinin-piperaquine (DP) is an artemisinin-containing, fixed-combination antimalarial drug developed in China. It has been evaluated extensively in clinical trials in Thailand, Vietnam, Cambodia, and China (Denis et al., 2002, Tran et al., 2004, Guo, 1993). Efficacy has been high and tolerability uniformly excellent in all trials in these multi-drug resistant areas including Cambodia and Vietnam (Denis et al., 2002, Tran et al., 2004), where PQP-resistance was common after extensive use. These trials have used a constant dose of PQP, but initially the co-formulation also included trimethoprim (CV8). This formulation (CV8) has been used extensively in Vietnam, where it is part of national policy. More recently the dose of DHA in DHA-PQP has been increased by 25%. This product (ArtekinTM) has been registered in China, Cambodia and Vietnam and in several countries in Africa including Senegal. DP is being used increasingly in Southeast Asia and is already part of national treatment recommendations in Cambodia and Vietnam. An alternative formulation of Artekin TM is being developed by the Medicines for malaria venture and should be ready for licensure in 2008.

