# *2.0 Objectives*

*2.1 Primary Objective*

To determine the safety and tolerability of AQ (three days) plus SP (one day), PQP (three days) plus SP (one day) and Artekin TM (PQP plus DHA) (3 days) when used for seasonal IPT in children.

*2.2 Secondary Objective*

To determine the efficacy of AQ (three days) plus SP (one day), PQP (three days) plus SP (one day) and Artekin TM (PQP plus DHA)(3 days) when used for seasonal IPT in children.

*3.0 Study design and methods*

*3.1 Study area*

The study will be based at the MRC Field Station in Basse in the Upper River Division (URD) of The Gambia. This is an area of savannah typical of much of sub-Sahelian Africa. Malaria transmission is seasonal, occurring mostly during the short rainy season (July - October), and is almost exclusively due to *P.* *falciparum*. *Anopheles gambiae* is the principal vector; the area has the highest entomological inoculation rate (EIR) in The Gambia (between 1 and 50 infective bites per person per year). The population has worked with the MRC for at least 20 years and cordial relations exist between the MRC and surrounding villages.

*3.2 Enumeration, recruitment and consent*

The study will be carried in collaboration with the National Malaria Control Programme and URD District Health Team and study children will be recruited from villages in the south bank of Upper River Division. During the preparatory phase of the study, the design and objectives of the study will be discussed extensively with the URD District Team and all health care providers working in the study area. The study team will visit all the villages in the study area to explain the objectives of the trial to village elders, opinion leaders and village health workers. This will be followed by village meetings, which the entire community will be invited to participate. During these meetings, agreement to participate in the study will be obtained from the villagers. In addition, parents or guardians of prospective study subjects in the right age group will be visited at home and they will be provided with flyers in English and the appropriate local language (Mandinka, Sarahule or Fula).

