# *3.11 End of malaria transmission season cross-sectional survey*

Children enrolled in the study will be seen at the OPD clinic at the end of malaria transmission season for examination by a study physician and a finger-prick blood sample will be obtained for preparation of a thick blood smear and determination of haemoglobin concentration. A standardized questionnaire will be administered to the parents/guardians of the study subject, to collect information regarding illness that had occurred since the last visit, symptoms experienced, use of healthcare facilities and use of medicines. Information on the use of bed nets will be collected again at this visit.

*3.12 Study end-points:*

*3.12.1 Primary end points*

*Safety endpoint*

- Incidence of any adverse events during the observation period.

*Secondary end points*

- Mean Hb (g/dl) at the end of malaria transmission.
- Prevalence of malaria parasitaemia at the end of the malaria transmission season.
- Number of OPD attendances with malaria that meet the case definitions as indicated below during the surveillance period.

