#### 3.13 Data management and analysis

All baseline, surveillance and laboratory data will be collected on forms designed for the trial. Field and laboratory staff will be trained to follow the procedures set out in a series of Standard Operating Procedures (SOPs). Key data will be double entered and inconsistencies checked; range checks will be used for standard variables. Primary analyses will be performed on an intention to treat (ITT) basis. Any child who receives a first dose of drug will be included in the ITT analysis. Children who are randomised but who do not receive any mediation will not be included in this analysis.

*3.14 Sample s-size calculations*

Drugs for IPT need to be acceptable and have low frequency of adverse events. If the frequency of adverse events is 20% in the SP/AQ group, a trial with 286 children per arm has 90% power to detect a halving in the frequency of adverse events, using a significance level of 0.05, or a reduction to 9% or less if a significance of 0.025 is used (to preserve an overall type 1 error rate of 5% for the primary endpoint when there are 2 comparisons, each alternative drug group with SP/AQ). If the frequency of adverse events is 15%, a reduction to 5% or less can be detected with the same power, and if the frequency is 10% a reduction to 2% or less can be detected. Based on experience from several studies the drop-out rate is not expected to exceed 15% and is likely to be less. Allowing for 15% drop out, a sample size of 286*3/(1-0.15)=1009 is needed.

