# *3.15 Ethical considerations*

The findings from this study could influence the choice of drug combination for IPTc in areas of seasonal transmission. Study children will benefit from the intensive follow-up during the study period. In addition, all malaria cases detected will be treated with an effective antimalarial. This study will not interfere with or limit access of study participants to the malaria prevention programme provided by the department of state for health. All of the drug combinations to be used in the study, amodiaquine plus SP, piperaquine plus SP and ArtekinTMm have been used extensively to treat or prevent malaria in young children and their safety profiles are well known.

*3.16 Oversight for the study*

A DSMB and Local safety monitor will provide oversight for the study

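### Section 3.14 limits the primary family to two tests at a fixed 0.025: this is valid, but it gives away power and leaves PQP+SP v Artekin without an error-controlled test, although the stated aim is to compare three combinations

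*Protocol*

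**What the plan says.** The rationale in section 1.2.3 takes SP+AQ as the starting point and says that "it is important to investigate if other drug combinations might be equally effective in preventing malaria but more effective in preventing adverse events". The aim follows directly: "Thus, we now propose to compare the safety, efficacy and tolerability of three potential drugs combinations for IPTc". Section 2.1 asks for the safety and tolerability of each of the three regimens and names no pair and no ranking. Section 3.6 randomises 1:1:1. The primary endpoint in section 3.12 is "Incidence of any adverse events during the observation period". Section 3.15 adds: "The findings from this study could influence the choice of drug combination for IPTc in areas of seasonal transmission".

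Section 3.14 fixes the error control. The reason it gives for the lower significance level reads: "to preserve an overall type 1 error rate of 5% for the primary endpoint when there are 2 comparisons, each alternative drug group with SP/AQ". With 286 per arm and SP/AQ at 20%, it claims 90% power for a halving at a level of 0.05, "or a reduction to 9% or less if a significance of 0.025 is used". PQP+SP v Artekin is not listed as a comparison, and no order of testing is given.

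**The concern.** The family that carries the 5% is narrower than the stated aim. If both alternatives turn out better tolerated than SP+AQ, the next question is which of the two to prefer. The randomised contrast that bears on it has no place in the primary inference. If it is added later without a rule, its error rate depends on how it is added.

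The fixed split also has a cost within the two planned tests. Section 3.14 reaches 90% power for a halving only at the unadjusted 0.05. At the adjusted 0.025 it needs a larger effect. With three groups, part of that loss can be recovered without weakening the 5% guarantee.

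**Working it through.** **Inputs from section 3.14:** SP/AQ rate 20%, halved to 10%; 286 per arm; 90% power; levels 0.05 and 0.025. Sidedness is not stated; two-sided is assumed because it reproduces 286.

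**The plan's own figure.** n = [z(α/2)·√(2·p̄·q̄) + z(β)·√(p1q1 + p2q2)]² / d², with p̄ = 0.15 and d = 0.10:
- (1.960 × 0.505 + 1.2816 × 0.5)² / 0.01 = 266
- continuity correction: (n/4)·[1 + √(1 + 4/(n·d))]² = 286, an exact match
- total: 858/0.85 = 1009.4, stated as 1009
- overall error bound: 2 × 0.025 = 0.05, correct for two tests

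**Power for the halving at 0.025.** [d·√286 − 2.2414 × 0.505] / 0.5 = (1.691 − 1.132)/0.5 = 1.12, so power is 86.8% (about 87% in simulation). For 20% v 9% at 0.025 the required n is 270 with continuity correction, so the plan's fallback statement holds.

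**Proposed rule.** Test each alternative v SP/AQ at 0.025. If at least one is significant, test every remaining pair, including PQP+SP v Artekin, at 0.05.

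**Why the overall error stays within 5%.**
- All three rates equal: a false rejection needs one of the two first tests to reject, so the bound is 0.025 + 0.025 = 0.05.
- Exactly one pair equal: that pair is tested at 0.05 at most.
- Exactly two pairs equal: impossible, because two equalities imply the third.

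Every rejection under the present rule is kept, so the new rule never rejects less.

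**Simulated familywise error** (286 per arm, two-sided pooled z-tests, all arms at 20%):
- present two tests, and the proposed rule: 4.7%
- two tests at 0.025 plus the third pair at 0.05 without any condition: 8.6%
- all three pairs at 0.05: about 12%

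**Simulated power.** Rates are SP/AQ, first alternative, second alternative. The alternatives' rates are assumptions, apart from the halving to 10%.

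| Rates (%) | Pair tested | Present rule | Proposed rule | 2-df closed test |
|---|---|---|---|---|
| 20/10/10 | SP/AQ v one alternative | 87% | 91% | 91% |
| 20/10/20 | SP/AQ v the effective one | about 87% | about 87% | 90.5% |
| 20/15/10 | SP/AQ v the better one | 87.5% | not below the present rule | 86.3% |
| 20/10/4 | between the alternatives | no test | 82% | 82% |
| 20/10/5 | between the alternatives | no test | 63% | 63% |
| 20/10/7 | between the alternatives | no test | 25% | 25% |

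The 2-df closed test means an overall three-arm test at 5%, then each pair at 5% if it is significant.

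**Simpler routes cost more.** Bonferroni over three pairs (0.05/3 = 0.0167) cuts power for 20% v 10% to 83% at 286 per arm and would need 362 per arm with continuity correction. Testing the third pair only after both alternatives beat SP/AQ at 0.025 controls the error, but gives 70% rather than 82% at 20/10/4, and 52% rather than 63% at 20/10/5.

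**The case against.** The strongest reply is that the two-comparison family is a coherent choice. The rationale measures new combinations against the regimen already used, the objectives ask for no ranking, and the remark about choice stands in the ethics section. All of that is right, and the 0.025 split is correct for the two tests it names. A reader might infer from the mismatch that the multiplicity control is wrong. The protocol does not support that: the limit is one of scope and efficiency.

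A reader might also infer that any test of PQP+SP v Artekin would break the 5%. It would if run unconditionally (8.6%). Run only after a planned rejection, it would not (4.7%).

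Nor does it follow that the trial has no way to choose. The arms are randomised 1:1:1, so the difference between the alternatives can be estimated, and section 3.12 plans haemoglobin, parasitaemia and malaria attendances as secondary endpoints.

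Finally, a further contrast may appear in an SAP that is not shown. The point therefore rests only on what section 3.14 itself fixes: the family and the split.

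Power, more than alpha, limits a choice between the alternatives. That stands, and no testing rule removes it.

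**Conclusion.** The point holds as a worthwhile improvement to section 3.14; it is not an error in the protocol's arithmetic. The present rule controls the error for two of the three pairs, gives 87% power for a halving at its own adjusted level, and has no controlled test of PQP+SP v Artekin. The proposed rule covers all three pairs within 5%. It raises power for a halving to 91% if both alternatives achieve it, and leaves it essentially unchanged if only one does.

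These figures assume two-sided tests, a binary endpoint per child, 286 evaluable children per arm and SP/AQ at 20%. The rates used for the contrast between the alternatives are not in the protocol; over the assumed range of 10% v 4% to 10% v 7%, power runs from 82% down to 25%.

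**What to change.** In section 3.14, keep the two tests of each alternative v SP/AQ at two-sided 0.025, and add that if at least one is significant, the remaining pairs, including PQP+SP v Artekin, are each tested at 0.05. State that with three groups this holds the overall type 1 error at 5%. The overall 2-df closed test is an acceptable alternative: it does better when only one alternative works and slightly worse in configurations such as 20/15/10.

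Add a sentence that the trial is not sized for PQP+SP v Artekin and that this difference will be reported with a confidence interval whatever the test shows.

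The cost is wording in section 3.14 and matching text in any SAP, with no extra children or data. The one downside is that PQP+SP v Artekin can be declared different only after at least one alternative differs from SP/AQ.
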